### 3.2. Primary Outcome Analysis

The primary outcome of our analysis is the incidence of intraoperative hypoxemia. The comparisons in hypoxemia incidence between the two groups will be evaluated with an χ^2^ test, and 95% CIs will be calculated for the difference in hypoxemia incidence.

### 3.3. Priori Subgroup Analyses

Known confounders have an impact on hypoxemia; therefore, subgroup analysis will be performed by comparing the main results for pre-defined subgroups. These include the preoperative pulmonary function test (mild vs. moderate or severe) and the preoperative partial pressure of oxygen (<80 vs. ≥80 mmHg), to eliminate the impact of these factors on hypoxemia.

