Heart rate (HR), SpO_2_, and noninvasive blood pressure (NIBP) are measured by an independent, blinded observer who collects research data at 3 min intervals. Patients are moved to the postanesthesia care unit (PACU) with oxygen support to maintain the oxygen saturation above 92%. Patients will be transferred to the PACU for Aldrete, delirium, and postoperative nausea and vomiting (PONV) assessment after awakening. The modified Aldrete score is used to assess the recovery from anesthesia and the return of psychotomotoric fitness. This validated assessment consists of 5 aspects (activity, respiration, blood pressure, consciousness, and SpO_2_), with a total score of 10. The clinical data on preoperative diagnosis, type of combined lung disease and blood gas, duration of bronchoscopy, and length of hospital stay are extracted from the medical record.

Safety will be assessed by interview and adverse event (AE) monitoring. All adverse events occurring during the whole study are recorded. Further follow-up is also necessary if there are clinical abnormalities.

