### 2.11. Sample Size Determination

Due to a lack of data from the literature, we were not able to estimate the differences between the three experimental conditions, which are necessary to calculate the sample size for a within-subject design. The sample size planned for this trial was based on the results of a pilot series preceding this research and on clinical judgment. The required sample size was calculated for the primary outcome and the incidence of perioperative hypoxemia. In our pre-experiment, the incidence of intraoperative hypoxemia was about 64% in the sufentanil group and 30% in the esketamine group. Given the 10% drop-out rate, the randomization of 33 individuals to each treatment group was required to achieve a level of significance and study power of 5% and 80%, respectively [35].

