### 3.4. Secondary Outcome Analysis

For secondary outcome analyses, the χ^2^ test or the Fisher exact test will be used for categorical variables, including the incidence of intraoperative hypotension or bradycardia, severe intraoperative hypoxemia rate, PONV, delirium, or postoperative fever. The Student’s *t*-test or the nonparametric test will be used for the awakening time, the total duration of intraoperative hypoxemia, and patient satisfaction.

Two-sided *p* values < 0.05 will be considered statistically significant. All statistical analyses will be performed using SPSS Statistics 26.0 and GraphPad Prism 7.

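### Subgroup comparisons are planned to remove the influence of lung function and PaO2, which they do not do; an adjusted analysis would serve that purpose, and the subgroups should be exploratory

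*Protocol article*

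**What the plan says.** Section 3.3 gives both the reason and the method: "Known confounders have an impact on hypoxemia; therefore, subgroup analysis will be performed by comparing the main results for pre-defined subgroups". The subgroups are "the preoperative pulmonary function test (mild vs. moderate or severe") and preoperative PaO2 below 80 versus 80 mmHg or more. The purpose is "to eliminate the impact of these factors on hypoxemia". The section states no pooled or adjusted estimate.

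Section 3.2 sets the primary analysis as a chi-square test of hypoxemia incidence, with a 95% CI for the difference. Section 2.5 describes 1:1 allocation in permuted blocks and names no stratification factor. Section 2.11 sizes the trial for the overall comparison only, at a 5% significance level and 80% power. It reports that "the incidence of intraoperative hypoxemia was about 64% in the sufentanil group and 30% in the esketamine group" in the pilot, and concludes: "Given the 10% drop-out rate, the randomization of 33 individuals to each treatment group was required". Section 3.4 adds "Two-sided *p* values < 0.05 will be considered statistically significant".

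On the source of the baseline values, section 2.7 points to the medical record: "The clinical data on preoperative diagnosis, type of combined lung disease and blood gas, duration of bronchoscopy, and length of hospital stay are extracted".

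**The concern.** The method does not match its stated purpose. Comparing the arms within PaO2 or lung-function subgroups asks whether the effect differs between patient types. Within a subgroup the factor is roughly held fixed, but the overall comparison is adjusted only if the subgroup results are pooled (as in Mantel-Haenszel) or the factor enters a model. The article states neither. It calls two factors important, sets out to remove their influence, and gives no step that does so.

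The word for them is also loose. Under randomisation they are prognostic factors that can be unbalanced only by chance; they are not confounders in the observational sense.

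Two things are at stake. First, if PaO2 predicts hypoxemia strongly, the crude test gives up some precision. Second, a reader who takes section 3.3 at its word may treat the subgroup p-values as the adjusted result. At this sample size a uniform effect will often look significant in one half of a factor and not in the other.

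**Working it through.** **Inputs.** From section 2.11: 64% versus 30% (difference 0.34), 33 per arm, 10% drop-out, alpha 5%, power 80%. From section 3.4: two-sided testing. Assumed, because the article does not give them: an even split of each factor, and the strength of PaO2 as a predictor.

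**1. The plan's own figure.** With unpooled variance:

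n = (1.960 + 0.842)² × (0.64×0.36 + 0.30×0.70) / 0.34² = 29.9, so 30 per arm.

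30 × 1.1 = 33, the stated number (30/0.9 = 33.3 would give 34). The size is reproduced, and it is for the overall comparison.

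**2. Power within a subgroup.** An even split of 33 gives 16.5 per arm, or about 15 after drop-out. With mean rate 0.47:

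power = Φ[(0.34√n − 1.96√(2×0.47×0.53)) / √(0.64×0.36 + 0.30×0.70)] = Φ[(0.34√n − 1.383) / 0.664]

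| Patients per arm | Power, approximation | Power, exact chi-square |
|---|---|---|
| 33 (whole trial) | 80% | 84% |
| 30 (whole trial after drop-out) | 76% | 77% |
| 16 | 49% | 50% |
| 15 | 46% | 46% |
| 10 (smaller part of an uneven split) | 32% | 31% |

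**3. What subgroup p-values would show under a uniform effect.** Suppose the true difference is 34 points in both halves of a factor, with 16 per arm in each. Then:

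- exactly one half significant: 2 × 0.486 × 0.514 = 50%;
- both halves significant: 0.486² = 24%.

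**4. Power of an interaction test.** For an interaction of 34 points (for example 64% versus 30% in one half, 47% versus 47% in the other) at 16 per arm, SE = √[(0.2304 + 0.2100 + 0.2491 + 0.2491)/16] = 0.242. Power = Φ(0.34/0.242 − 1.96) = 29%. Other layouts with 15 to 16.5 per arm give 27% to 33%. The proper test is therefore weak too, so the subgroups can only be exploratory.

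**5. Chance imbalance.** For a factor present in 50% of patients, an imbalance of 20 points or more at 33 per arm means a gap of at least 7 patients. The exact binomial probability is 10.9%. With an assumed odds ratio of 5 to 8, a 20-point imbalance shifts the crude difference by about 6 to 9 points.

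**6. What adjustment would gain.** Simulation with 20,000 runs, 30 per arm, one binary factor at 50% prevalence, and marginal rates held at 64% and 30%:

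| Assumed odds ratio of the factor | Chi-square | Cochran-Mantel-Haenszel | Change (points) |
|---|---|---|---|
| 1 | 77.2% | 76.4% | −0.8 |
| 3 | 77.7% | 79.1% | +1.4 |
| 5 | 78.2% | 81.9% | +3.7 |
| 8 | 77.3% | 84.5% | +7.2 |

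Type I error of the adjusted test was 4.8% to 5.3%. A separate simulation stratified by two factors lost 2 to 3 points against chi-square at odds ratios of 1 and 2. That favours adjusting for one factor only.

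**The case against.** The strongest reply is that the primary analysis needs no repair. That stands. A reader might infer from section 3.3 that the unadjusted chi-square is confounded or invalid. It is not: in a 1:1 randomised trial its error rate and confidence interval already allow for chance imbalance, and the sample size rests on the same two crude proportions. Adjustment is a gain in efficiency.

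A reader might also infer that the gain is free. It is not. It depends on odds ratios that the article does not supply, and it turns slightly negative if PaO2 is not prognostic. It also needs PaO2 for every patient. Blood gas comes from the medical record, the visit schedule in Table 1 lists no blood gas, and the procedure takes place in an outpatient room, so some values may be missing.

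The subgroup sizes rest on an even split, and low subgroup power is usual. The article claims no power for these comparisons and does not say that it will draw efficacy conclusions from them. This stands as a limit on the harm. It does not rescue the stated purpose.

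It would go too far to conclude that lung function is not collected because the extraction list in section 2.7 omits it. Section 3.3 itself names the test, and a condensed article may shorten a list. Likewise, the split into mild versus moderate or severe leaves patients with normal function unplaced, although the criteria in sections 2.3 and 2.4 do not require impairment. This may be shorthand, and it needs only a clarification.

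An unseen analysis plan may contain an adjusted analysis or an interaction test, so their absence here is not the point. The aim stated in section 3.3 would still be wrong.

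**Conclusion.** The point holds in a limited form. Section 3.3 states a wrong purpose: subgroup comparisons do not eliminate the influence of PaO2 or lung function on the treatment comparison, and the primary test and the allocation as described use neither factor.

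The subgroup results cannot carry separate conclusions. With an even split, power is about 46% to 50% at the full planned effect, and a uniform effect would be significant in exactly one half of a factor about half the time. A less even split makes the smaller subgroup weaker still.

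Adjusting for PaO2 is a better-matched and low-cost way to meet the stated aim. It changes power by about −1 point to +7 points across assumed odds ratios of 1 to 8, at 30 evaluable patients per arm and 50% prevalence. The primary chi-square, its interval and the sample size are not invalidated.

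**What to change.** 1. Delete the clause about eliminating the impact of these factors, and call them prognostic factors.
2. Before unblinding, pre-specify a Mantel-Haenszel risk difference, or a logistic model with a standardised risk difference, adjusted for PaO2 below 80 versus 80 mmHg or more. Make it the primary analysis, or at least the key supportive one, and report the crude chi-square alongside. Give patients with missing PaO2 an unknown stratum so that nobody is dropped.
3. Label the subgroups exploratory. Report a treatment-by-subgroup interaction test and within-group differences with CIs, and draw no conclusion from separate subgroup p-values.
4. Define the lung-function grouping as normal or mild versus moderate or severe.

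**Cost.** Changes of analysis wording and no extra patients. The price is about 1 point of power if PaO2 is not prognostic, and the work of obtaining PaO2 for every patient.

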### 3.4. Secondary Outcome Analysis

For secondary outcome analyses, the χ^2^ test or the Fisher exact test will be used for categorical variables, including the incidence of intraoperative hypotension or bradycardia, severe intraoperative hypoxemia rate, PONV, delirium, or postoperative fever. The Student’s *t*-test or the nonparametric test will be used for the awakening time, the total duration of intraoperative hypoxemia, and patient satisfaction.

Two-sided *p* values < 0.05 will be considered statistically significant. All statistical analyses will be performed using SPSS Statistics 26.0 and GraphPad Prism 7.

## 4. Discussion

Our trial aims to compare the effect of esketamine/propofol versus sufentanil/propofol on the incidence of hypoxemia in patients undergoing bronchoscopy, thereby providing a better safety and satisfaction plan during bronchoscopy. Given the rise in interventional therapy, bronchoscopy under general anesthesia may become more frequent in the coming future, and this research may provide a safe anesthesia management option for its implementation.

## Figures and Tables

**Figure 1 jcm-11-04587-f001:**
[figure not shown]
Study enrollment. SpO_2_, oxygen saturation; PONV, postoperative nausea and vomiting.

**Table 1 jcm-11-04587-t001:** Flow chart of the study. PACU, postanesthesia care unit; POD, postoperative day; CAM, the Confusion Assessment Method; PONV, postoperative nausea and vomiting. “×” means perfoming in that time.

Items	Visit 1	Visit 2	Visit 3	Visit 4	Visit 5
Time	One day before bronchoscoy	Morning of bronchoscopy	During bronchoscopy	PACU	POD1
Eligiblility screen	×				
Medical history and medication history	×				
Surgery history	×				
Physical examination	×				
Inclusion/exclusion criteria	×	×			
Informed consent		×			
Randomization		×			
Demographics			×	×	
Hemodynamic variables			×	×	
Study drug			×	×	
Outcome indicators			×	×	×
CAM				×	×
Aldrete				×	
PONV				×	×
Adverse events			×	×	×
Patient satisfaction					×

**Table 2 jcm-11-04587-t002:** Definitions of the multiple outcomes included in this study protocol. SpO_2_, oxygen saturation; PONV, postoperative nausea and vomiting.

Outcome	Definition	Instrumental/Tool
Incidence of intraoperative hypoxemia	The rate of SpO_2_ < 90% lasts for 30 s during the bronchoscopy.	SpO_2_
Hemodynamic stability and safety	Cardiovascular adverse events such as hypotension or bradycardia, which will be measured as a change >25% from baseline and/or necessitating an intervention.	Non-invasive blood pressure and electrocardiogram
Awakening time	Time from end of bronchoscopy to Aldrete score of 9.	Aldrete
Severe intraoperative hypoxemia	SpO_2_ < 75% at any time during the bronchoscopy.	SpO_2_
Total duration of intraoperative hypoxemia	Total duration of SpO_2_ < 90% during the bronchoscopy.	SpO_2_
PONV	The severity of PONV (none, mild, moderate, and severe).	Likert scale
Delirium	To evaluation of a patient’s delirium status within 3 days after bronchoscopy.	The Confusion Assessment Method
Adverse events	Accidental or adverse reactions to sedatives that threaten or cause patient injury or discomfort	World SIVA International Sedation Task Force Tool
Patient satisfaction	Patient satisfaction with the procedure experience (very unsatisfied, unsatisfied, satisfied, very satisfied)	Likert scale

## Data Availability

Not applicable.

## Abbreviations

SpO_2_: oxygen saturation; SPIRIT: Standard Protocol Items: Recommendations for Interventional Trials; CONSORT: Consolidated Standards for Trial Reporting; TCI: target-controlled infusion; ASA: American Society of Anesthesiologists; PONV: postoperative nausea and vomiting; AE: adverse event; CAM: Confusion Assessment Method; CIs: confidence intervals.
